### Secondary outcomes

The study will have three evaluations of secondary outcomes: limitations during ADL performance, functional exercise capacity, and peripheral muscle strength. These outcomes will be evaluated before and after the intervention period as well as after the post-intervention follow-up period of 3 months.

#### Limitations during activities of daily living

Limitations during the performance of ADLs will be evaluated by the LCADL scale, developed by Garrod et al. (2000) [42], translated to Portuguese, and validated for use in COPD in Brazilian patients [32, 33]. This scale contains 15 items divided into four domains: personal care (four items), domestic (six items), physical activity (two items), and leisure (three items) [33]. The total score can vary from 0 to 75 points, and the higher the score, the greater the limitation in ADLs [32].

#### Functional exercise capacity

Functional exercise capacity will be evaluated through the 6MWT, performed in accordance with the guidelines established by the ATS [43].

#### Peripheral muscle strength

Measurement of muscle strength will be performed in the dominant member by using a Force Gauge digital dynamometer, (Instrutherm - model DD-300), and the results will be expressed in newtons. The patient will be instructed to perform the movements of elbow flexion and knee flexion and extension, resisted by a steel cable coupled to the dynamometer. The measurement will be repeated five times with an interval of 1 min between attempts, and the highest value among the three closest measurements will be recorded [44].

### Sample size calculation

This is a superiority trial in which sample size determination was performed through prior study [45] information based on the primary PADL variable. With the expectation of an increase in the number of steps of 45% (approximately 2260 steps) in the FTG compared with the CTG and UTG (both with no expected increase), using a standard deviation of 2603 steps, and loss at follow-up of 20% of individuals (values commonly found in the study population) [44], 25 individuals will be required in each of the three groups to obtain a power of 80%, adopting an α of 5%.

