**Methods:**

In this randomized controlled trial, patients with COPD will be randomly assigned (1:1:1) to an 8-week training program to follow one of the three *a priori* defined groups: (I) resistance and aerobic and functional exercises, (II) a conventional program including only resistance and aerobic exercises, or (III) a usual care program. Patients will be evaluated before and upon completion of 8 weeks of training regarding physical activity in daily life (PADL) using an activity monitor (accelerometer), activities of daily living (London Chest Activity of Daily Living), functional exercise capacity (6-minute walk test), and muscle strength (dynamometry). Additionally, the sustained effects of the interventions will be evaluated 22 weeks after commencing the study.

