### Statistical analysis

The statistical program SPSS 22.0 (IBM, Armonk, NY, USA) will be used. The data will be submitted to the normality test of Kolmogorov–Smirnov, and if they present normal distribution, the descriptive variables will be expressed as mean and standard deviation; if they do not fit the Gaussian distribution model, data will be presented as median and interquartile range. Mauchly’s sphericity test will be performed. Once the sphericity is assumed, two-way analysis of variance (ANOVA) will be performed to evaluate the possible intra- and inter-group differences (FTG, CTG, and UCG) at pre-intervention, post-intervention, and post-*follow-up*. The Tukey post-hoc will be used to identify the specific differences in the variables in which the F values found are higher than the established statistical significance criterion. To evaluate the effect size between interventions, Cohen’s d test will be used. The level of significance adopted will be 5%. Data integrity will be monitored by regularly scrutinizing data files for omissions and errors. Participants will be given an anonymous study ID to protect confidentiality, and only study investigators will have access to the final trial data set.

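### The stated 80% power holds for an unadjusted two-group or omnibus test; the planned Tukey comparison of FTG with CTG has about 63% to 75%

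*Protocol article*

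**What the plan says.** The article's Sample size calculation section sets the effect as follows: "With the expectation of an increase in the number of steps of 45% (approximately 2260 steps) in the FTG compared with the CTG and UTG", with the two comparators described as "both with no expected increase". It continues "using a standard deviation of 2603 steps, and loss at follow-up of 20% of individuals", and concludes that "25 individuals will be required in each of the three groups to obtain a power of 80%, adopting an α of 5" per cent. It names neither the test nor whether that test is one- or two-sided, and it does not say whether the SD is that of a step count or of a change in step count.

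The Statistical analysis section plans a two-way ANOVA over three groups and three time points. For pairwise differences it says: "The Tukey post-hoc will be used to identify the specific differences in the variables in which the F values found are higher" than the significance criterion. No other pairwise between-group test is given.

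The Analysis of the population section replaces missing assessments with the patient's latest available one, under intention to treat. The Introduction frames the aim as the effect of adding a functional circuit to combined aerobic and resistance training. That is the FTG-versus-CTG contrast.

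**The concern.** A power figure belongs to a particular test. The sample size paragraph gives 80% without naming one, and the analysis paragraph names a stricter pairwise procedure than the one that reproduces the sample size. An omnibus F test over three groups can be significant without showing that FTG differs from CTG, so the trial's conclusion on its main question rests on the Tukey step.

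If that step has about 63% power, a true 2260-step benefit would be missed about 37% of the time rather than 20%. A null result would then be read against an assurance that the design does not give for that comparison.

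**Working it through.** **Inputs from the article.** Difference 2260 steps; SD 2603; 20% loss; 25 per group; α 5%; Tukey over three groups. **Assumed:** two-sided tests, and 2603 as the SD of the analysed variable in a single contrast. Standardised effect: d = 2260/2603 = 0.868.

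**Reproducing the stated figure**

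- Two-group normal approximation: n = 2(1.960 + 0.842)²/d² = 20.82 per group. Multiplied by 1.2 this is 24.99, so 25, the stated size.
- With 20% lost, 25 × 0.8 = 20 remain. Power by normal approximation: Φ(0.868 × √(20/2) − 1.960) = Φ(0.786) = 78.4%.
- Omnibus F, means (2260, 0, 0), n = 20: noncentrality 20 × (2/3) × 0.868² = 10.05, on 2 and 57 degrees of freedom, power 79.5%.

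**The loss allowance.** Multiplying by 1.2 does not fully offset a 20% loss. The need is 21 evaluable per group (normal) or 22 (t test), and 20 remain. Dividing by 0.8 gives 21/0.8 = 26.3, so 27, or 22/0.8 = 27.5, so 28.

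**Power for FTG versus CTG.** The noncentrality is 0.868 × √(n/2): 2.746 at n = 20 and 3.070 at n = 25.

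| Test | 20 per group | 25 per group |
|---|---|---|
| Two-group t | 76.3% | 85.3% |
| t with three-arm pooled error | 77.0% | 85.7% |
| Tukey, three groups | 63.4% | 74.9% |

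The Tukey critical values on the t scale are 2.406 (57 df) and 2.393 (72 df). If a significant F is also required, the Tukey figure at 20 per group is 62.9% by simulation. Tukey reaches 80% at 28 evaluable per group, or 28/0.8 = 35 randomised.

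**Carry-forward.** Assume that the lost 20% carry forward a value with no gain and that the SD is unchanged. The mean difference is then 0.8 × 2260 = 1808, with 25 per group analysed. Power is 67.2% (t) and 52.8% (Tukey).

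**If 2603 is the SD of a step count and the analysis adjusts for baseline.** The residual SD is 2603 × √(1 − ρ²), where ρ is the correlation between baseline and outcome. The article gives no ρ, so a range is shown (three-arm pooled error, one covariate).

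| Assumed ρ | Tukey, 20 per group | Tukey, 25 per group | Single unadjusted contrast, 20 per group |
|---|---|---|---|
| 0.3 | 68% | 79% | 81% |
| 0.5 | 77% | 87% | 88% |
| 0.7 | 92% | 97% | 97% |

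**The case against.** The strongest reply is that the stated size is not an arithmetic error. The usual two-group formula, with 20% added, gives exactly 25, and the omnibus F test that heads the planned analysis has 79.5% power at 20 per group. That stands. A reader might infer that 25 per group is miscalculated, or that 80% can be recovered only from the F test; the article's own inputs support neither. The 76% to 77% from the t test reflects t rather than z and a slightly lenient loss allowance, a matter of 2 to 3 patients per group.

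Second, 20 evaluable per group is a complete-case premise, whereas the article carries the latest assessment forward and so nominally analyses 25. This also stands, and is why 75% is shown beside 63%. It does not rescue the claim: Tukey stays below 80% at 25 per group, and carried-forward values without gain would lower power further.

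Third, the Tukey figure depends on what the SD describes. If 2603 is the SD of a step count, a baseline-adjusted analysis could bring Tukey near or above 80%. But the analysis paragraph specifies no baseline adjustment, and the article gives no correlation to support one.

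Fourth, the article never claims 80% power for Tukey in so many words. That is true, but it offers no other pairwise test for the comparison that its sample size paragraph describes.

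**Conclusion.** The point holds in a limited form. The 80% is approximately right for an unadjusted two-group test or the omnibus F test, and the loss allowance leaves only a minor shortfall. It is not right for the planned route to an FTG-versus-CTG conclusion. Under the stated inputs, Tukey power is about 63% with 20 evaluable per group and about 75% with all 25 contributing undiluted data. It is about 53% if losses are carried forward with no gain, which is an assumption.

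All three figures rest on two-sided testing, a Tukey family of three groups and 2603 as the SD of the analysed variable. Under baseline adjustment, with 2603 as the SD of a step count, the figure at 20 per group would range from 68% to 92% for correlations of 0.3 to 0.7.

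A reader might also infer that the trial must enlarge to 35 per group, or that success requires FTG to beat both comparators. The article sets no joint-success rule, and the discrepancy can be resolved without more patients.

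**What to change.** Keep 75 patients and do one of the following.

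1. In the Sample size calculation section, state that the 80% refers to an unadjusted two-group or omnibus test. Say whether 2603 is the SD of a step count or of a change, and report the Tukey power for FTG versus CTG (about 63% to 75%) under that assumption. Cost: one paragraph reworded and a less favourable stated power.
2. Prespecify one baseline-adjusted FTG-versus-CTG contrast at two-sided 5% as the primary comparison, and keep Tukey for the other comparisons. Both the sample size and the Statistical analysis sections must then change. If 2603 is the SD of a step count, power at 20 per group is about 81%, 88% and 97% for assumed correlations of 0.3, 0.5 and 0.7, and the assumed correlation should be stated. Cost: a small change to the analysis paragraph.

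Under either option, the loss allowance should be described as leaving 20 per group, slightly short of the 21 to 22 that the unadjusted calculation needs.

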### Statistical analysis

The statistical program SPSS 22.0 (IBM, Armonk, NY, USA) will be used. The data will be submitted to the normality test of Kolmogorov–Smirnov, and if they present normal distribution, the descriptive variables will be expressed as mean and standard deviation; if they do not fit the Gaussian distribution model, data will be presented as median and interquartile range. Mauchly’s sphericity test will be performed. Once the sphericity is assumed, two-way analysis of variance (ANOVA) will be performed to evaluate the possible intra- and inter-group differences (FTG, CTG, and UCG) at pre-intervention, post-intervention, and post-*follow-up*. The Tukey post-hoc will be used to identify the specific differences in the variables in which the F values found are higher than the established statistical significance criterion. To evaluate the effect size between interventions, Cohen’s d test will be used. The level of significance adopted will be 5%. Data integrity will be monitored by regularly scrutinizing data files for omissions and errors. Participants will be given an anonymous study ID to protect confidentiality, and only study investigators will have access to the final trial data set.

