Sewell et al. [28] demonstrated improvement in PADL and ADL performance after a short-term training program combining functional exercises with aerobic and home training in patients with COPD. Despite the benefits obtained, the authors did not evaluate whether the responses were maintained for a longer period of time than the program period and did not include the progressive resistance training, an essential component for these patients. It is still unknown whether the addition of a functional circuit training (structured on the basis of the limitations during ADLs) to a conventional combined aerobic and resistance training program, commonly performed and well established in PR programs, can improve PADL, ADL performance, and functionality of patients with COPD in the short term. In addition, it is unknown whether possible functional and PADL gains obtained in this type of training are maintained during a 3-month follow-up.

This randomized clinical superiority trial aims to evaluate the effects of the addition of a circuit of functional physical training to an 8-week combined training (aerobic and resistance) on PADL, ADL performance, functional exercise capacity, and peripheral muscle strength of patients with COPD. In addition, the effects of the interventions will be re-evaluated 3 months after the training completion. It is hypothesized that the proposed functional training will lead to behavioral changes, influencing the improvement in the performance of ADLs and, consequently, PADL, accompanied by functional improvement in patients with COPD.

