## Discussion

### Potential impact and significance of the study

The present proposal was developed through extensive literature research on this topic. Through the interpretation of the results found in several studies, it was possible to develop this concise and structured training protocol. The use of this protocol in the treatment of COPD will confirm whether the addition of functional physical training to a conventional training will promote positive effects on PADL and functionality and whether there will be maintenance of possible gains at the 3-month post-training follow-up.

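### The aim needs FTG versus CTG, but the analysis does not make that contrast decisive, and F-then-Tukey gives it about 63% power, not 80%

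*Protocol article*

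**What the plan says.** The Introduction calls this a superiority trial that "aims to evaluate the effects of the addition of a circuit of functional physical training to an 8-week combined training (aerobic and resistance"). The Discussion (Potential impact and significance of the study) says that use of the protocol "will confirm whether the addition of functional physical training to a conventional training will promote positive effects on PADL and functionality". Both describe the increment of FTG over CTG.

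The trial has three arms: "patients with COPD will be randomly assigned (1:1:1) to an 8-week training program". Under Interventions, the usual care arm receives respiratory physiotherapy and no exercise training.

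The Sample size calculation assumes a gain of 45%, about 2260 steps, an SD of 2603 and 20% dropout. It words the comparison as a gain "in the FTG compared with the CTG and UTG (both with no expected increase"). I read the printed UTG as UCG. The result is 25 per arm for 80% power at 5%. The two comparators are named together, with no statement of whether FTG must beat both, either or one in particular.

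The Statistical analysis section gives the tests: "two-way analysis of variance (ANOVA) will be performed to evaluate the possible intra- and inter-group differences (FTG, CTG, and UCG"). Three visits enter this analysis: baseline, end of training and the 3-month assessment. Tukey comparisons follow where F is significant. One 5% level covers everything. No arm pair, visit or interaction term is identified as deciding superiority.

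**The concern.** Three kinds of result could come out of this analysis as significant: a change within FTG, a difference between FTG and UCG, and a difference between FTG and CTG. They answer different questions. A change within FTG mixes the circuit with everything else that happens over 8 weeks. FTG versus UCG mixes the circuit with the effect of exercise training as a whole. Only FTG versus CTG isolates what the circuit adds.

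The two between-arm contrasts have the same expected size only if CTG gains nothing, as the sample size assumes. If CTG does gain, they separate, and the plan does not say in advance which one settles the question.

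There is also a power consequence. Tukey spreads the 5% over three arm pairs, so the contrast that matters is tested more strictly than an unadjusted comparison. The unstated both-or-either rule then moves the power further.

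**Working it through.** **Inputs from the Sample size calculation.** Difference 2260 steps; SD 2603; loss 20%; α 5%; power 80%; 25 per arm. Evaluable per arm: 25 × 0.8 = 20.

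**Assumptions.** The test is two-sided (not stated). The SD of 2603 applies to the quantity compared between arms (the document does not say whether it is of levels or of change). Data are normal with equal variances.

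**1. Reproducing 25 per arm.**
- Pairwise, unadjusted: n = 2 × (1.960 + 0.842)² × (2603/2260)² = 20.8. Multiplying by 1.2 gives 25.0. Rounding up to 21 and dividing by 0.8 gives 26.25, so 27.
- Omnibus F with means (2260, 0, 0) and n = 20: noncentrality = 20 × [(1506.7)² + 2 × (753.3)²] / 2603² = 10.05, which gives 79.5% power. Then 20 / 0.8 = 25.

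The stated figure therefore fits either an unadjusted pairwise test or the omnibus F. The calculation does not reveal which contrast was meant to decide.

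**2. Power in the design scenario (only FTG gains 2260), 20 evaluable per arm.** The standardised difference is 2260/2603 = 0.868, and the noncentrality is 0.868 × √(20/2) = 2.75.

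| Decision rule | Power |
|---|---|
| FTG > CTG, F then Tukey | about 63% |
| FTG beats both CTG and UCG, F then Tukey | about 48% |
| FTG beats either CTG or UCG, F then Tukey | about 78% |
| FTG–CTG alone, unadjusted 5%, two-arm t-test (38 df) | 76.3% |
| FTG–CTG alone, unadjusted 5%, variance pooled over three arms (57 df) | 77.0% |

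The first three rows are simulated (200,000 trials: F at 5%, then Tukey with q(3, 57) = 3.40). The last two are noncentral t. The Tukey critical value on the t scale is 3.40/√2 = 2.41, against 2.00 for the single contrast with 57 df. That difference accounts for the loss from about 77% to about 63%.

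**3. What happens if CTG gains as much as FTG and UCG gains nothing.** Same rule, 20 per arm, 200,000 simulated trials for each row.

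| Shared gain in FTG and CTG | FTG > UCG significant | FTG > CTG significant |
|---|---|---|
| 1000 steps | about 12% | about 1% |
| 1130 steps (half of 2260) | about 15% | about 1% |
| 1500 steps | about 28% | about 1% |
| 2260 steps | about 63% | about 1% |

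In every row the circuit adds nothing to conventional training. The shared gains are assumptions, chosen to show the range.

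I put no percentage on within-arm changes. How often FTG changes significantly while CTG does not depends on the pre–post correlation and on which F (interaction or time main effect) must be significant before Tukey is used. The plan fixes neither.

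**The case against.** The strongest reply is that the question is already fixed. The Introduction and the Discussion both pose the effect of adding the circuit, so FTG versus CTG can be inferred as the intended contrast. The sample size speaks only of between-arm comparisons, and Cohen's d is planned between interventions. Mentioning differences within and between groups is ordinary language for a group-by-time ANOVA. A condensed article may also leave the ranking of contrasts to a fuller document.

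Most of this stands. A reader might infer that the plan accepts a within-arm change, or a win over usual care, as proof that the circuit works. The document nowhere says so, and it sets no success rule of any kind. Nor is this mainly inflation of false positives, since Tukey controls error across the arm pairs. It is also fair that the 63% in the last row of the second table needs CTG to gain the full 2260 steps. The sample size assumes no gain, and the Introduction describes the evidence for activity gains after rehabilitation as mixed, particularly for short programmes. Finally, maintenance of gains to follow-up is legitimately an over-time question, so within-arm reporting has its place.

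The reply does not remove the mismatch. The article does state its tests, and as stated they do not single out the contrast that its aim needs. That the contrast can be inferred does not stop another significant result from being presented as the answer. Nor does it explain a stated power of 80% when the stated procedure gives about 63% for that contrast.

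**Conclusion.** The point holds as a mismatch between aim and analysis, and it is worth correcting. The aim needs FTG minus CTG; the analysis does not make it decisive; the sample size leaves open whether FTG must beat both comparators or either.

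The size has two parts. First, under the design's own assumptions with 20 evaluable per arm, F-then-Tukey gives about 63% power for FTG versus CTG, with 48% to 78% depending on the unstated both-or-either rule, against the stated 80%. Second, if CTG shares FTG's gain, FTG beats UCG in about 12% to 63% of trials for gains of 1000 to 2260 steps, with FTG above CTG in about 1%.

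The power figures rest on reading SD 2603 as the SD of the compared quantity and on a two-sided test. The second set also rests on assumed gains in CTG. The textual mismatch depends on neither. The conclusion stops at a risk left open: it is not that the plan would declare the circuit effective on a within-arm or FTG–UCG result.

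**What to change.** In Statistical analysis, state that:
- superiority is decided by one between-arm contrast, FTG minus CTG in change in daily steps from baseline to the end of the 8-week training (group-by-time or baseline-adjusted), tested at two-sided 5% and reported with its 95% CI;
- FTG versus UCG and CTG versus UCG are supporting comparisons;
- within-arm changes may be reported, including for maintenance of gains at follow-up, but cannot support a claim about the circuit.

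In Sample size calculation, name FTG versus CTG as the powered contrast and restate its power as about 76% at 20 evaluable per arm. Daily steps is the natural measure because the sample size is already expressed in it.

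The cost is a few sentences, with no new data or patients. Power for the deciding contrast rises from about 63% to about 76–77% at the same size. The small downside is that a within-arm or FTG–UCG result can no longer be presented as the trial's positive finding.

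### Baseline steps enter the two-way ANOVA as an outcome level, not a covariate, and the deciding F test is not named: unbiased, but less efficient than baseline adjustment

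*Protocol article*

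**What the plan says.** The Statistical analysis section fixes the model: "two-way analysis of variance (ANOVA) will be performed to evaluate the possible intra- and inter-group differences (FTG, CTG, and UCG) at pre-intervention", followed by the post-intervention and post-follow-up visits. It comes after Mauchly's test and is introduced by "Once the sphericity is assumed", so visit is a repeated factor with three levels and the pre-intervention value is one of them. Tukey comparisons follow for any variable with a significant F. The section does not say whether that F is for group, visit or their interaction. The article mentions no baseline covariate and no change-from-baseline analysis.

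The Sample size calculation section describes a superiority trial. It expects an "increase in the number of steps of 45% (approximately 2260 steps) in the FTG" and none in the conventional training group (CTG) or usual care group (UCG), "using a standard deviation of 2603 steps", with "loss at follow-up of 20% of individuals", and concludes that "25 individuals will be required in each of the three groups" for 80% power at a 5% level. It gives no pre-post correlation and does not say whether the SD is that of a single visit or of a change.

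The Study design and Primary outcome sections have patients wear the accelerometer for 7 days before training, so baseline steps are collected by design.

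**The concern.** Treatment cannot affect a value measured before it starts. Treating that value as an outcome therefore spends information that would otherwise reduce residual variance. Step count appears to vary widely between patients: the planned gain implies a mean near 2260 / 0.45 = 5022 steps, and the stated SD, if it is a single-visit SD, is about half of that.

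Because the deciding F is not named, the plan also leaves open how much is lost. The interaction F spreads its 4 degrees of freedom over three groups and three visits, and does not isolate the functional circuit group (FTG) against CTG at week 8. The group main effect averages over all visits, including the one at which randomisation makes the expected difference zero. In a trial of 75 patients these choices can move power well away from the planned 80%.

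**Working it through.** **Inputs.** From the Sample size calculation section: difference δ = 2260 steps, SD σ = 2603, 25 per group, 20% loss, so 25 × 0.8 = 20 evaluable per group. Assumed, because the document does not give them: σ applies at each visit; correlation ρ = 0.3, 0.5 or 0.7 between any two visits; two-sided 5% with no multiplicity adjustment.

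**The plan's own figure.** n = 2(1.960 + 0.842)² × (2603 / 2260)² = 2 × 7.849 × 1.327 = 20.8, so 21 evaluable per group. Allowing for loss, 21 / 0.8 = 26.25, so 27; the looser 21 × 1.2 = 25.2 gives 26. The stated 25 is within two patients of both. With 20 evaluable, an unadjusted comparison of post-intervention values has 78% power (76% with the t distribution), and a one-way three-group F has 79.5%.

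**SD that enters each FTG-CTG contrast.**
- Change from baseline: σ√(2(1 − ρ)) = 3080 / 2603 / 2016.
- ANCOVA at week 8: σ√(1 − ρ²) = 2483 / 2254 / 1859.
- Mean of three visits: σ√((1 + 2ρ)/3) = 1901 / 2125 / 2328.

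The variance ratio of ANCOVA to change is (1 − ρ²) / (2(1 − ρ)) = (1 + ρ)/2 = 0.65 / 0.75 / 0.85. It is below 1 for every ρ < 1, whatever σ is.

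**Expected difference under the group main effect.** If the gain is fully kept: (0 + 2260 + 2260)/3 = 1507 steps, or 2/3 of δ. If it is lost by follow-up: 2260/3 = 753 steps, or 1/3 of δ.

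**One case by formula (ρ = 0.5, normal approximation).** Power = Φ(difference / (SD√(2/20)) − 1.96).
- Change: 2260 / 823 = 2.75, power 78%.
- ANCOVA: 2260 / 713 = 3.17, power 89%.
- Main effect, gain kept: 1507 / 672 = 2.24, power 61%.

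The table allows for small samples, which lowers the first two slightly.

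**Power with 20 per group** (simulated under compound symmetry; simulation error and the choice of error term move entries by up to about two points):

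| Test | ρ = 0.3 | 0.5 | 0.7 |
|---|---|---|---|
| ANCOVA, FTG vs CTG, week 8 | 79% | 86% | 95% |
| ANCOVA, three-group F, week 8 | 83% | 90% | 98% |
| Change contrast, FTG vs CTG, week 8 | 63% | 76% | 93% |
| Interaction F (4 df), gain kept | 69% | 84% | 98% |
| Interaction F, half the gain kept | 55% | 68% | 92% |
| Group main-effect F, gain kept | 71% | 62% | 54% |
| Group main-effect F, gain lost by follow-up | 23% | 19% | 15% |
| Tukey FTG vs CTG on visit means, gain kept | 54% | 45% | 36% |

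The like-for-like comparison for the interaction F is the three-group ANCOVA F. The loss is 83 − 69 = 14, 90 − 84 = 6 and 98 − 98 = 0 points if the gain is kept, and 28, 22 and 6 points if half is kept.

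**If 2603 is a change SD instead.** The ANCOVA residual SD becomes 2603√((1 + ρ)/2) = 2099 / 2254 / 2400. The change contrast then has 76% power at every ρ, and ANCOVA has 91 / 87 / 83%.

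**The case against.** The strongest reply is that the planned analysis is valid. In a randomised trial a group-by-visit ANOVA gives an unbiased comparison, and its interaction F tests whether groups change differently. That fits the stated aims: a gain after training, and whether it lasts to three months. On that reading the pre-treatment visit dilutes nothing, and at a correlation of 0.7 almost no power is lost if the gain is either kept or lost. This stands, and it limits the point to efficiency and to the unnamed test.

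A reader might infer from the low main-effect and Tukey figures that the trial is badly underpowered. The document does not support that. Nowhere does it say that superiority rests on means averaged over visits, and listing the three visits reads at least as naturally as comparison by visit or over time. Those figures are conditional on one reading that the text leaves open.

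Two further inferences also fail. The absence of a fallback if Mauchly's test rejects is detail that a condensed article commonly leaves to the full plan, and nothing shows that sphericity will fail. Within-group differences are listed, but superiority is not rested on them, and they bear on whether gains are maintained.

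Finally, neither the correlation nor the meaning of the SD is given, so the size of the loss cannot be fixed. Its direction against a change contrast can, because the variance ratio (1 + ρ)/2 does not depend on the SD.

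**Conclusion.** The point holds as one of efficiency and of an undefined deciding test. The plan commits to a model that uses baseline as an outcome, although adjusting for it would be more precise and needs no extra data. Under the stated assumptions, ANCOVA gains about 16, 10 and 2 percentage points over a change contrast at correlations of 0.3, 0.5 and 0.7. Against the interaction F the loss is material at low correlation or if only half the gain persists, and small or nil at 0.7. Power falls far below 80% at every correlation shown only if the group main effect, or Tukey on visit-averaged means, is what decides.

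The randomised comparison is not biased, and this point does not make 25 per group wrong. The figures rest on 20 evaluable per group, equal correlation between visits and, except where stated, a per-visit SD of 2603.

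**What to change.** Name as primary analysis a baseline-adjusted between-group comparison of steps per day at week 8. Either an ANCOVA or a mixed model will do; the latter would take week 8 and follow-up as outcomes and baseline as covariate. State that the adjusted FTG-CTG and FTG-UCG differences in steps per day, with 95% confidence intervals, are the deciding contrasts. The mixed model also gives the follow-up differences that address maintenance. State what the SD of 2603 measures, so that the power of the adjusted analysis can be checked.

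The cost is one degree of freedom and a few rewritten lines in the Statistical analysis section. No new data, visits or patients are needed.
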